### Ethics and dissemination

This study has obtained ethical clearance from the Ethics Review Committee (ERC), Faculty of Medicine, University of Colombo, Sri Lanka (EC-23–121). Progress review will be conducted by ERC every six months until the trial is complete, where progress of the ongoing trial activities, any changes in the protocol and challenges will be reviewed and discussed. There is no specific trial steering committee allocated to this trial, other than the Data Monitoring Board (DMB). This board comprises two professors who are permanent staff members of the Faculty of Medicine, University of Colombo and with specialized areas of biochemistry and statistics. They are neither investigators of this project nor have any competing interests. The contact details of these members will be shared with the study participants requesting them to contact for any concerns. The DMB will independently review the queries and compile a report which will be reviewed along with the progress of the trial by the ethics review committee. Further, the amendments to the protocol will be immediately notified by the PI to the Sri Lankan Clinical Trials Registry in which the trial is registered; and if relevant, to the trial participants and regulators.

The food being tested in this intervention has been consumed by Sri Lankans for decades, and the preliminary survey has indicated no adverse effects*.* The food safety assessments carried out have already confirmed its compliance with reference safety values*.* Moreover, *diyabath* for the intervention will be produced according to an SOP, ensuring compliance with all relevant general hygienic practices. The total microbial counts, counts of pathogenic indicators and the heavy metal content will be tested in randomly collected samples of *diyabath*. Further, venipuncture will be carried out by an experienced nurse. Therefore, no adverse events are anticipated during implementation of the trial. However, participants will be provided with contact information of the investigators, an independent medical officer and DMC members to report any allergies, adverse events or changes experienced in the appetite, stool consistency, frequency and other concerns following consumption. The information sheet provided will also indicate the ingredients that are used in *diyabath* recipe (rice, coconut milk, red onion, roasted chilli, black pepper powder) so that those with allergies could refrain from participating in the study. Given these precautions, the intervention is expected to pose zero to minimal harm to participants.

The collected data will be stored as hard copies in a locked cupboard at the Faculty of Medicine, University of Colombo and in a password protected electronic database for at least 5 years. Confidentiality of the collected data will be assured. All the collected biological samples and data will be coded and analysed. The names of participants will not be used for any purpose other than to send their test reports. For any new analysis to be done using bio banking, ethics approval as well as re-consenting would be done.

The study findings will be disseminated in scientific publications regardless of the magnitude or direction of effect. If required, access to the participant level-data and statistical code will be decided upon on case-by-case basis, upon the recommendation of the ERC and DMB.

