## Methods

### Study design

This protocol is for a single arm, non-randomized, controlled trial (Fig. 2) reported in accordance with the SPIRIT statement. This design will ensure that factors, such as gut flora, digestion and other physiological variables, which could influence the study results, remain consistent in participants throughout the study period, as the same group of participants will serve as both the control and test groups. This consistency will enable reasonable comparisons with minimum effect due to individual differences. A wash-out period is not considered in the design, as *diyabath* is introduced as the intervention only after the initial control phase.

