**Fig. 3 Fig3:**
[figure not shown]
Time structure of the trial

Primary outcomes of the study include changes in the following parameters:*Host gut microbiome composition:* Evaluated using percentage abundance of probiotic strains (i.e. *Lactobacillus* spp, *Bifidobacterium* spp) and other beneficial microorganisms (i.e. *Oscilllospira*, *Akkermansia muciniphila*), alpha-diversity index and firmicutes-to-bacteroidetes ratio (F/B). Diversity index reveals the change in the gut microbiome composition and is important to have a balanced ratio between the most common two phyla (Firmicutes and Bacteroidetes F/B) for homeostasis of the gut [38]. Gut microbiota is directly responsible to develop digestive, immunological and metabolic functions in host [39, 40].*Nutritional status and health parameters*: Evaluated by serum micronutrients and serum ferritin*Health biomarkers*: Assessed by lipid profile, high-sensitivity C-reactive protein (hsCRP), fasting blood sugar (FBS), aspartate aminotransferase (AST), alanine aminotransferase (ALT) and serum insulin*Immune markers:* Evaluated by analysing interleukin-6 (IL-6), IL-10 and cytokines

Each participant is expected to improve these parameters to either reach a healthy limit or a healthier end if already in the healthy limit.

Secondary outcomes of the study include:*Antioxidant capacity:* An increase in total antioxidant capacity in serum after consumption of an antioxidant rich food indicates absorption of antioxidants from the food and an enhanced in vivo defence status against oxidative stress [41].*Anthropometry:* Measured as waist circumference, hip circumference and BMI

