**Fig. 4 Fig4:**
[figure not shown]
CONSORT flow chart for the trial

**Table 1 Tab1:** Participant timeline

Task	Study period (weeks)													
	**Recruitment**	**Non-intervention control period**						**Intervention period**					**Post-intervention follow up**	
ENROLLMENT - Eligibility screening - Informed consent	−2	0^a^	2	4	6	8	10^b^	12	14	16	18	20^b^	21	22^b^
	X													
	X													
Maintaining a food diary (24 h dietary records)		x	x	x	x	x	x	x	x	x	x	x	x	x
Baseline control assessment		x												
Anthropometry (height, weight, Waist circumference, Hip circumference, BMI)		x					x					x		x
Collection of blood samples (fasting) - serum micronutrients & serum ferritin - serum lipid profile - serum free fatty acids - AST, ALT - hsCRP, IL-6, IL-10, Cytokines - FBS & serum insulin		x					x					x		x
Collection of stool samples - Gut microbiome analysis (% abundance, alpha-diversity index, F/B ratio) - Short chain fatty acid profile		x					x					x		x

^a^assessment is done at the beginning of the week

^b^assessment is done at the last day of the week

Participants will be informed not to take part in any other nutritional intervention as well as not consume any nutritional supplementations including other cooked rice-based fermented foods during the study. A list of such food items will be given to them for reference at the beginning of the study. In addition, each participant will be asked to record daily all the foods that they have eaten other than what is provided by the hostel throughout the intervention phase. These records will be checked by an investigator during weekdays. Set reminders will be sent daily via SMS to all participants to keep records of their diets and will be asked to acknowledge the receipt of the message.

During the intervention period, every morning, the participants will be reminded via SMS to be present at the breakfast table. Standard portions of *diyabath* will be placed in the dining area before breakfast, ensuring uniformity in presentation across all participants. One investigator will be present at the site to observe the participants, to ensure that they consume *diyabath* as intended and answer any queries. The participants are requested to finish the served amounts and return the containers. If there is any leftover *diyabath*, the investigator will weigh it and make a record of it. This procedure will be repeated daily for 10 weeks during the intervention phase.

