#### Discontinuation of the intervention

Participants of the study can voluntarily withdraw their consent and participation at any time during the study. In addition some participants would be compelled to take antibiotics or nutritional supplements during this period. In such instances, those who took antibiotics for 5 days or more will be discontinued. The discontinuation of those who started taking any nutritional supplement during the course of intervention will be considered case by case. Further, based on the dietary data records, participants who consumed other fermented cooked rice- based food for more than 4 days during the study period will be also discontinued from the study. In addition to that, participants will be discontinued from the study if they report any adverse events that may produce lethal outcomes.

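### Symptom-type adverse events rest on spontaneous report with unequal prompting between phases, so complaints cannot be compared fairly between the control and diyabath phases

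*Protocol article*

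**What the plan says.** The Protocol article describes safety reporting mainly under Ethics and dissemination. Participants receive contact information for the investigators, an independent medical officer and the monitoring members "to report any allergies, adverse events or changes experienced in the appetite, stool consistency, frequency and other concerns following consumption". The same section has a second, general channel to the Data Monitoring Board: "The contact details of these members will be shared with the study participants requesting them to contact for any concerns". For what arrives that way, "The DMB will independently review the queries and compile a report", which goes to the ethics committee. The stated expectation is "Therefore, no adverse events are anticipated during implementation of the trial".

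Under Discontinuation of the intervention, stopping for harm also depends on the participant speaking up: "participants will be discontinued from the study if they report any adverse events that may produce lethal outcomes".

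Under Implementation, the diyabath meal is supervised: "One investigator will be present at the site to observe the participants", with the further task of answering queries. No equivalent presence is described for the control phase. Table 1 lists the scheduled tasks and has no symptom or stool-habit row in any period. It does schedule a food diary from week 0 to week 22.

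Under Study design, the comparator is each woman's own earlier phase: "the same group of participants will serve as both the control and test groups".

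**The concern.** The plan names the complaints it thinks worth hearing about: allergy, appetite, stool consistency and stool frequency. Apart from allergy, these are common, fluctuating complaints that also occur without diyabath, so they need a background rate to be interpretable. The control phase could supply one. The Statistical analysis section gives that phase the task of revealing seasonal, physiological or climatic change. For symptoms, however, the chance that a complaint is voiced and written down differs between the phases.

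This can mislead in two directions. If few women make contact, the silence may be taken as tolerability, although nobody was asked. If some women complain during the diyabath phase, the excess over the control phase may reflect only the extra prompting and the investigator at the table. There is also a hidden route. A woman who eats less diyabath because of discomfort, and tells nobody, is counted under Compliance and drop-outs as a drop-out (70% or less of the total dose), not as a harm. The Discussion foresees promoting diyabath in the community if outcomes are successful, so a usable description of tolerability would be wanted by then.

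**Working it through.** **The two phases side by side**

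| Feature | Control phase | Diyabath phase |
|---|---|---|
| Specific invitation to report symptoms | Worded around consumption; diyabath is first given after T1 | Applies directly |
| General contact with the board | Available, self-initiated | Available, self-initiated |
| Investigator on site at the meal | None described | Yes, observing and answering queries |
| Scheduled symptom questions (Table 1) | None | None |
| Food diary | Scheduled in Table 1; the Implementation text mentions daily food recording only for the intervention phase | Scheduled in Table 1 and in the text |
| Laboratory markers | T0 and T1 | T1 and T2, then T3 |

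Only the last row is a like-for-like comparison by design. The symptom rows are either unequal or empty.

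**Number of women.** The plan gives no figure for harms; the only one used here is the sample size. Its formula gives {31×69 + 73×27} × 7.9 / 42² = 4110 × 7.9 / 1764 = 18.41. Doubling gives 36.81 (36.82 in the article), and adding 25% gives 46.0, against a stated 45. I use 45; the one-woman difference does not affect this point.

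**Illustration 1: a false excess from unequal capture.** All rates are assumptions. Let b be the background complaint rate per 10-week phase, equal in both phases (no true harm), and let r_c and r_i be the shares of complaints recorded in the control and diyabath phases. Phases are taken as independent.

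- Expected reports: 45·b·r_c and 45·b·r_i.
- Discordant probabilities: p10 = b·r_i(1 − b·r_c) and p01 = b·r_c(1 − b·r_i).
- The number of discordant women is Binomial(45, p10 + p01). Given that number, those with a diyabath-only report are binomial with probability p10/(p10 + p01).
- A false excess is a two-sided exact McNemar p ≤ 0.05 in the direction of more reports under diyabath.

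| b | r_c / r_i | Expected reports, control / diyabath | Probability of a false excess |
|---|---|---|---|
| 10% | 50% / 50% | 2.25 / 2.25 | 0.3% |
| 10% | 10% / 60% | 0.45 / 2.7 | 3.4% |
| 10% | 0% / 50% | 0 / 2.25 | 2.4% |
| 20% | 50% / 50% | 4.5 / 4.5 | 0.9% |
| 20% | 10% / 60% | 0.9 / 5.4 | 26% |
| 20% | 0% / 50% | 0 / 4.5 | 29% |
| 30% | 50% / 50% | 6.75 / 6.75 | 1.2% |
| 30% | 10% / 60% | 1.35 / 8.1 | 53% |
| 30% | 0% / 50% | 0 / 6.75 | 69% |

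The zero-capture rows can be checked by hand. With no control reports, significance needs at least 6 diyabath reports, because 2 × 0.5⁶ = 0.031 while 2 × 0.5⁵ = 0.0625.

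**Illustration 2: what silence is worth.** If none of 45 women reports a complaint, the one-sided 95% upper limit for the reporting probability is 1 − 0.05^(1/45) = 6.4%. The limit for the true complaint rate is that figure divided by the capture share: 6.4% with full capture, 6.4/0.5 = 12.9% with half, and 6.4/0.25 = 25.8% with a quarter. Under spontaneous report the capture share is unknown, so no limit can be stated.

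**The case against.** The strongest reply is that the article condenses a fuller protocol, that adverse events are neither a primary nor a secondary outcome, and that no phase comparison of complaints is planned. On that view nothing in the stated analysis is broken, and prompted rather than spontaneous reporting is a preference. Part of this stands. The absence of an adverse-event form or grading scheme from an article is not a finding, and the planned outcome tests are untouched. What remains is the method the article does state: a self-initiated route, prompted more in one phase than in the other.

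Three stronger readings are tempting, and the documents do not support them.

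- A reader might infer that adverse events are invited only in the diyabath phase. The request to contact the board for any concern is not tied to consumption or to a phase. In the other sentence, the reference to consumption may qualify only the last items of the list.
- A reader might infer that the trial has no control-phase comparison for any harm. AST, ALT, hsCRP, fasting blood sugar and lipids are measured alike at T0 to T3, and changes are tested in both phases against a null of zero, so a worsening mean would show as well as an improvement. A table of women crossing laboratory reference limits is ordinary analysis-plan detail, and its absence here is no finding.
- A reader might infer that the control phase will yield almost no reports. No document gives a reporting rate, and the open channel argues against assuming zero.

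The remark about minimal expected harm is a forward-looking risk statement to the ethics committee, not a conclusion drawn from silence.

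**Conclusion.** The point holds for symptom-type adverse events only. Followed as written, the plan gives no like-for-like record of appetite, stool and allergic complaints across the phases. Complaint counts should not be compared between phases, and a low count is not evidence of tolerability. The laboratory markers and the planned outcome analyses are not affected.

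The direction of the problem follows from the text; its size does not. In the unequal-capture scenarios above, the chance of a false excess runs from 2.4% to 69%, against about 1% or less with equal capture. The large values need a background rate of 20% or more together with little or no capture in the control phase. This is a low-cost improvement worth making, not an error that invalidates the trial.

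**What to change.** - Add a few fixed questions to the diary that Table 1 schedules in every period, covering appetite, stool frequency and consistency, abdominal symptoms and allergic symptoms. Ask them with the same wording and at the same interval in the control, intervention and follow-up periods.
- Confirm that the diary runs in the control phase. Table 1 says it does, but the Implementation text mentions daily food recording only for the intervention phase, so the two must be reconciled.
- Report the within-woman comparison of control and intervention phases descriptively as a safety outcome: women with each complaint in neither phase, one phase only, or both. Keep spontaneous reports in a separate listing.
- Put this in place before T0, because the control-phase record cannot be recovered afterwards. If that phase has already begun, state in the report that complaint counts are not comparable between phases and that few reports do not show tolerability.

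The cost is a few diary lines and one table. The downside is slightly more burden for participants and more mild events reported in both phases, which should be said when the results are presented.

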## Discussion

There is currently no scientific data available on traditional fermented rice-based pre-breakfast meals like *diyabath*, making it essential to gather traditional knowledge about it from community and indigenous medical practitioners and to scientifically evaluate its properties and functionality, in order to develop interventions that are of practical value in low-resource countries where rice constitutes the staple diet. This methodology could serve as a model to evaluate other indigenous food in the future.

One of the major challenges in interventions based on traditional food is maintaining the consistency in its composition and texture. To address this, the trial plans to strictly adhere to the developed SOP. However, since the fermentation can still vary depending on the environmental conditions such as temperature, especially when conducted domestically, therefore, *diyabath* for the intervention will be prepared in the same place throughout the study. Furthermore, to check whether microbial composition of *diyabath* drastically, samples of *diyabath* provided for the intervention will be analysed randomly during the study.

Previous studies have reported considerable variability over time in the patterns of gut microbiome diversity among individuals undergoing the same food-based intervention [7]. This variability may be due to differences in metabolic conditions, such as inflammation levels. Therefore, using same participants as the test and control groups will minimize the impact of factors such as food preferences, individual metabolism and other physiological variables on the comparisons between test and control groups, revealing the true impact of the intervention on each individual.

The percentage presence of *Oscillospira* at baseline vs at the end of the intervention was considered for the sample size calculation from a previous study which was conducted to evaluate the impact of fermented and high fiber food consumption on gut microbiome composition [7]. Of the reported organisms in the microbiome studies *Oscillospira* was identified as a genera which is constantly detected by 16S rRNA gene surveys of the human microbiome [46]. Furthermore, it has been identified that the abundance of *Oscillospira* is positively correlated with the diversity of gut microbiota [54]. It has been associated with improved markers of health and negative correlations with gut related diseases [54, 55]. Therefore, detection of the presence of *Oscillospira* is considered a reliable marker to evaluate the health of gut. The calculated sample size is compatible with previous studies that report significant changes between the pre-post consumption of fermented and other food on gut microbiota compositional, health, immune and nutritional parameter [43, 56–58].

Moreover, this design will include provisions to minimize the impact of consuming other fermented or similar foods. Such consumption by study participants will be closely monitored. In the information sheet, participants will be informed to refrain from taking fermented cereal foods as much as possible during the intervention period. The consumption of other types of fermented foods, such as yogurt will be reviewed through 24-h food re-call records. Furthermore, if any considerable deviation from the hostel menu is revealed, impact of these confounders will be analysed case by case using comparison of the results from the control period with those from the intervention period.

If successful outcomes are shown, this intervention programme will be promoted among the community and especially among young women of reproductive age. This will help highlight and popularize *diyabath,* which is currently less recognized as a low-cost, sustainable and nutritive solution for enhancing the health status of Sri Lankan women. The results are applicable to other Asian countries of similar socio-cultural backgrounds, where rice is the staple food.

### Trial status

Protocol version has been approved by the the Ethics Review Committee of the Faculty of Medicine, University of Colombo, Sri Lanka (Ref: EC-23–121-2.1.1). Further, this trial has been registered in the Sri Lanka Clinical Trials Registry (SLCTR): SLCTR/2024/032 (Registration date: 09/10/2024).

## Data Availability

No datasets were generated or analysed during the current study.

## Abbreviations

IMP: Indigenous medical practitioners
WHO: The world health organization
SOP: Standard operating procedures
SLSI: Sri Lankan standard institute
SLS: Sri Lankan standards
MRS: De Man–Rogosa–Sharpe agar
FASSAI: Food Safety and Standards Authority of India
FDA: Food and Drug Administration (US)
HACCP: Hazard analysis and critical control points
AOAC: Association of Official Analytical Chemists
HPLC: High-performance liquid chromatography
ICP-MS: Inductively coupled plasma mass spectrometry
GC: Gas chromatography
ITI: Industrial Technology Institute
SCFA: Short chain fatty acids
NGS: Next generation sequencing
BMI: Body mass index
SD: Standard deviation
FFQ: Food frequency questionnaire
HsCRP: High-sensitivity C-reactive protein
FBS: Fasting blood sugar
AST: Aspartate aminotransferase
ALT: Alanine transaminase
IL: Interleukin
PUFA: Poly unsaturated fatty acids
ISAK: International Society for the Advancement of Kinanthropometry
CLIA: Chemiluminescence immunoassay
ABTS: Azino-bis-(3-ethylbenzothiazoline-6-sulfonic) acid
ERC: Ethics review committee
DM: Data monitoring committee
CTRSL: Sri Lanka Clinical Trial Registry
